## Abstract

**Background:**

Smoking in pregnancy remains a public health challenge. Nicotine replacement therapy (NRT) is effective for smoking cessation in non-pregnant people, but because women metabolise nicotine and cotinine much faster in pregnancy, it is unclear whether this will be effective for smoking cessation in pregnancy. The NHS Health Technology Assessment Programme (HTA)-funded smoking, nicotine and pregnancy (SNAP) trial will investigate whether or not nicotine replacement therapy (NRT) is effective, cost-effective and safe when used for smoking cessation by pregnant women.

**Methods/Design:**

Over two years, in 5 trial centres, 1050 pregnant women who are between 12 and 24 weeks pregnant will be randomised as they attend hospital for ante-natal ultrasound scans. Women will receive either nicotine or placebo transdermal patches with behavioural support. The primary outcome measure is biochemically-validated, self-reported, prolonged and total abstinence from smoking between a quit date (defined before randomisation and set within two weeks of this) and delivery. At six months after childbirth self-reported maternal smoking status will be ascertained and two years after childbirth, self-reported maternal smoking status and the behaviour, cognitive development and respiratory symptoms of children born in the trial will be compared in both groups.

**Discussion:**

This trial is designed to ascertain whether or not standard doses of NRT (as transdermal patches) are effective and safe when used for smoking cessation during pregnancy.

## Background

Maternal smoking during pregnancy harms unborn children and, as up to 30% of pregnant women smoke [1], it is a significant public health problem. The adverse effects of smoking during pregnancy include an increased risk of miscarriage and stillbirth, accounting for 4000 deaths annually, and of pre-term birth and low birth weight leading to increased perinatal morbidity [2,3]. Children of mothers who smoke whilst pregnant are at increased risk of neo-natal mortality, sudden infant death syndrome and asthma [2]. Maternal smoking whilst pregnant is also associated with an increased risk of attention deficit and learning problems in childhood [3,4]. Currently only around 25% of pregnant smokers stop for even part of their pregnancy and, of these, around two thirds re-start post-natally [1].

Effective methods for promoting smoking cessation by pregnant women are required. The most effective smoking cessation therapy in non-pregnant smokers is a combination of behavioural support and pharmacotherapy with either nicotine replacement therapy (NRT) [5] or bupropion [6]. Behavioural support alone can increase smoking cessation rates by up to 7% [7] and the addition of pharmacotherapy increases this further by 1.5 to 2-fold. Behavioural support is usually provided without pharmacotherapy, however, because of concerns that drug therapy may harm the fetus [8]. This is understandable for bupropion, but is far less logical for nicotine.

Pregnant women who smoke will already expose their unborn children to nicotine. Nicotine has well documented potential adverse effects in pregnancy, since it is a vasoconstrictor and nicotine from cigarettes causes dose-related increases in maternal blood pressure and heart rate and has lesser effects on the fetal heart rate [9]. In rats chronic nicotine exposure is associated with dose-dependant alterations in behavioural and cognitive responses, CNS toxicity and a diminished adrenal response to hypoxia that, in humans, could pre-dispose to sudden infant death syndrome [9]. Consequently, nicotine may also be responsible for the attention deficit and learning problems that are described above [4]. Cigarette smoke, however, contains numerous other toxins in addition to nicotine and it is not known which of these actually cause harm, though the fetal effects of nicotine have been most widely studied. The cardiovascular effects of nicotine from NRT are less than those observed from smoking and regular NRT use generates lower plasma nicotine concentrations (when body weight is accounted for) than those in the animal experiments described above [9]. There is also no evidence that NRT use in pregnancy results in higher plasma nicotine concentrations than smoking [9]. For these reasons, and because using NRT in pregnancy results in exposure to only nicotine and no other toxins, there is expert consensus that NRT use is safer than smoking in pregnancy as long as pregnant women using NRT do not receive more nicotine from NRT than they would have done by smoking [10,11]. It is difficult, though, for health professionals to give clear guidance to pregnant women on using NRT when the safety of NRT in pregnancy is justified primarily on theoretical grounds and its efficacy has not been established.

To date, evidence on the effectiveness of NRT in pregnancy comes from 3 studies and is inconclusive [12-14]. Two of these studies were trials investigating NRT as transdermal patches. [12,13]. but one [13] was stopped after only 40 patients had been randomised. The other [12], however, randomised 250 women but produced no clear evidence that NRT was effective, since the odds ratio for smoking cessation using NRT versus placebo was 1.1 with a 95% CI of 0.7 to 1.8. This odds ratio is much lower than that obtained from meta-analysis of trials of NRT patches in non-pregnant subjects (OR, 1.74) [5] and raises questions about whether using NRT in pregnancy is effective for smoking cessation. The third study was not placebo controlled and randomised women to intensive behavioural support with an additional option to use NRT patches and/or gum).)[14] or a 'normal care' group which received only very minimal smoking cessation advice. Although, 75 women in this trial opted to use NRT, this design makes it difficult to disentangle any effect of NRT from that of intensive behavioural support. Where reported, no harmful effects of NRT were demonstrated in these 3 studies. In the larger patch trial [12], babies born in the NRT group were significantly heavier than others [mean birth weight (adjusted for prematurity) difference = 186 g (95%CI 35,336 g)], suggesting that pure nicotine as NRT has less impact on fetal growth in utero than smoking. Additionally, in the trial which allowed a group of women to use either NRT patches or gum or a combination of these, mean birth weights in fetuses born after 37 weeks were not statistically different between the 2 trial groups [non-significantly lighter (by 32 g) in NRT group]. In both trials that reported the distribution of low birth weight infants between groups [12,14], no significant differences were noted.

It has recently become apparent that conventional doses of nicotine contained in NRT may be insufficient for pregnant women and this may explain the negative findings from the one trial of NRT in pregnancy. In pregnancy, the metabolic clearances of nicotine and cotinine (the principal metabolite of nicotine) are increased by 60% and 140% respectively. [15]. Accordingly, even when pregnant women take standard doses of NRT for adequate periods, these may still be ineffective because they may require higher doses of NRT to replace the nicotine they would have received via smoking. Higher doses of NRT might, therefore, be needed in pregnancy, but because there is very little human-subject research into the effects of nicotine on the developing fetus, it is not known whether these might increase the risk of fetal damage. Until the effectiveness of the current conventional dose of NRT is established, it is hard to justify trials of higher ones.

In summary, although consensus opinion suggests that taking NRT during pregnancy is likely to be safer than smoking [8,10,11,16], there is little direct trial evidence to support this and we do not know if NRT is actually *effective *in promoting smoking cessation amongst pregnant smokers. The *SNAP *trial will produce direct evidence on these important questions and will investigate whether or not NRT is more effective than placebo in achieving smoking cessation for women who and are between 12 and 24 weeks pregnant, who currently smoke 5 or more cigarettes daily and who smoked 10 or more cigarettes daily before pregnancy.

## Methods/Design

Ethical approval to conduct this study from the Oxfordshire REC A ethics committee (ID number 04/Q1604/85)

### Treatment group

Pregnant women will receive an eight week course of 15 mg/16 hr NRT transdermal patches. Although many studies have used longer courses, there is no evidence that these are more effective [5]. Patches will be issued in conjunction with individual behavioural support (*Section 10*) which is an effective smoking cessation intervention in pregnancy [7]. Four weeks after their quit dates, women who are not smoking will be issued with a second four week supply of patches.

### Control group

Women in the control arm of the trial will receive an identical placebo NRT patch and the same behavioural support as those in the treatment group. In both control and intervention groups, participants will be blind to their group allocation.

### Randomised procedure

After collecting pre-randomisation baseline data, exhaled carbon monoxide readings will be taken from women and assuming that readings indicate that women do smoke [cut off 8 ppm [17]], informed consent for trial entry will be sought. After consenting to trial entry, women will receive an initial behavioural support session before being randomised. Full details are given later.

Randomisation will be via the Nottingham Trials Unit web-based database and randomisation service. In each centre the recruiting research midwife (RM) will have a username and password. (S)he will log on to the trial website that hosts the trial database, confirm that the patient eligibility criteria are all met and enter an agreed minimum amount of *registration *data about the participant and centre before randomisation is possible. Data to be entered at this stage are described later. The computer will then issue a trial number which will be the unique identifier for the trial participant and a trial pack number which will reflect the treatment allocated. Randomisation will be stratified by trial centre only.

Numbered packs of active and placebo patches will be distributed by Queens Medical Centre pharmacy and stored in all participating ante-natal/ultrasound clinics. After randomisation, the research midwife will select the patch pack with the appropriate number and issue this to the participant. The research midwife and the trial participant will both be blind to group allocation. The research midwife will issue NRT/placebo under the supervision of a senior, local doctor via a patient group directive (PGD) [18]. When research midwives visit women at home to enrol them into the trial, immediate internet randomisation will not be possible. In this circumstance the research midwife will return to her/his hospital base to randomise the enrolled woman and the appropriate trial pack will be posted to the trial participant.

### Outcome measures

These relate to smoking, fetal loss, fetal and maternal morbidity and health economic outcomes.

Primary end point: Self-reported, prolonged and total abstinence [19] from smoking or the use of any non-pharmacological nicotine containing substances between a quit date set within two weeks of randomisation and immediately prior to childbirth.

Prolonged abstinence cannot be comprehensively validated, but if participants report prolonged abstinence and are abstinent at ***both ***time points below, they will be considered tohave a positive primary outcome. This is **one **outcome requiring **three **different measures to be achieved.

i) Self reported smoking cessation for at least 24 hours before follow up at one month after quit date, ***validated by ***exhaled CO measurement [cut off 8 ppm [17]].

ii) Self reported smoking cessation for at least 24 hours before hospital admission for childbirth, ***validated by ***exhaled CO measurement [cut off 8 ppm [17]].

Secondary end points:

#### a) Smoking

1. Self reported, prolonged abstinence [19] from smoking between quit date and one month.

2. Self reported, prolonged abstinence [19] from smoking between quit date and 6 months after delivery.

3. Self reported smoking cessation for previous 7 day period at 6 months after delivery (point prevalence) [19].

4. Self reported, prolonged abstinence [19] from smoking between quit date and 2 years after delivery.

5. Self reported smoking cessation for previous 7 day period at 2 years after delivery (point prevalence) [19].

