#### c) Upon admission for childbirth

The following data are recorded by the RM or delivery suite staff:

Date of follow up/exhaled CO reading or saliva sample

Smoked at all in the 24 hrs prior to delivery

Smoked between quit date and delivery

One or both of, *i) exhaled CO reading & ascertainment date ii) saliva sample *(for cotinine)

On how many days have patches been used?

On how many days (if any) have non-trial patches been used?

How many behavioural support sessions with NHS stop smoking services used (telephone & face to face)?

i) These data obtained by RM from ***maternal ***or ***infant medical records before ***discharge. For reasons of data protection some personal infant details are recorded on paper rather than being transmitted over the internet to the trial database:

*maternal *

hypertension (>140/90) on 2 occasions (excluding labour)

miscarriage (between randomisation and 24 weeks)

labour onset (spontaneous, induced, no labour)

mode of delivery (SVD, instrumental, caesarean)

ante natal or post natal maternal hospital admission

*infant*

baby initials

D.O.B

Gender

Baby NHS number

*Prompt for RM to confirm full name and address and contact details of baby and to record these on paper *(see below)

Prompt for RM to make a new record of contact details if these have differed from previous (i.e. maternal) ones

baby hospital number

birth weight

Number of births

if multiple birth, indicate number and birth order

live or stillbirth?

cord ph < 7.0

Apgar <7 at 5 min

*Gestational age at birth *– to be calculated within database from gestation at recruitment

These infant personal details will be recorded on paper only:

baby name

baby address (inc postcode)

ii) These data obtained by research midwife from ***infant medical records after ***discharge:

If live birth? live on leaving hospital

ventilation > 24 hrs

necrotising enterocolitis

neonatal convulsions

admitted to special care

*intraventricular haemorrhage *(4 categories)

*congenital abnormality present (y/n). If y then free text to describe this*.

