### General statistical analysis plan

#### a) Primary outcome measure

The proportion of women who report prolonged and total abstinence from smoking immediately before child birth will be compared between treatment groups by Chi-squared test, on an intention to treat basis (all those randomised) with smokers lost to follow up considered to have continued smoking. For this analysis, we will assume that women in each group use their allocated treatments as directed and no randomised participants will be excluded from analyses. Baseline data on smoking behaviour and demographic information will be compared between groups, and adjustment made for any differences, using logistic regression.

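### The 6-month and 2-year prolonged-abstinence outcomes rest on self-report alone and are not tied to the CO-validated pregnancy result, so a woman who fails the primary outcome can still count as continuously abstinent

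*Protocol article*

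**What the plan says.** Under Outcome measures, the primary end point is "Self-reported, prolonged and total abstinence [19] from smoking or the use of any non-pharmacological nicotine containing substances between a quit date" and the time just before childbirth. The article accepts that self-report needs support: "Prolonged abstinence cannot be comprehensively validated, but if participants report prolonged abstinence and are abstinent at" both of two time points, the outcome is positive. The first is one month after the quit date. The second is delivery, worded as "Self reported smoking cessation for at least 24 hours before hospital admission for childbirth". Each is validated by exhaled CO with a cut-off of 8 ppm, and all three measures must be met. The analysis plan for the primary outcome adds an intention-to-treat rule, "with smokers lost to follow up considered to have continued smoking".

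Under Secondary end points, a) Smoking, outcome 2 is "Self reported, prolonged abstinence [19] from smoking between quit date and 6 months after delivery" and outcome 4 is "Self reported, prolonged abstinence [19] from smoking between quit date and 2 years after delivery". Neither mentions CO or requires that the primary outcome was met. The data collection lists for 6 months, 1 year and 2 years give the maternal smoking item only as smoking status, and they include no biological sample. No section says that the validated status at delivery is carried forward into outcomes 2 and 4.

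**The concern.** The time windows are nested but the criteria are not. Abstinence from quit date to 6 months or 2 years implies abstinence from quit date to delivery. The trial tests that earlier stretch biochemically and then leaves the test out of the longer outcome.

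Take a woman who says she has not smoked since her quit date but reads 15 ppm at delivery. She fails the primary outcome. If she repeats the claim at 6 months, she succeeds on an outcome whose window includes the day of that reading. A woman with no CO reading at one month or at delivery is in the same position, because the primary outcome needs all three measures.

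The effect on the comparison has a predictable direction. True sustained quitters become fewer after birth, whereas women who misreport need not stop doing so. Women who failed validation can therefore make up a larger share of the long-term count than their share of reported abstainers at delivery. If smokers misreport equally often in both arms, this raises both rates and moves their ratio towards 1.

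**Working it through.** **The plan's own figures.** The Sample size section gives 16% v 25%, 500 per arm, two-sided 5% and 93% power. A normal-approximation calculation gives 94.2%, which is close enough. For a 7-point difference (16% v 23%) it gives 79.9%, against the stated 80%. An odds ratio of 1.74 applied to 16% gives 24.9%. The article states no figure for outcomes 2 and 4, so what follows is illustration only.

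**Inputs**
- Delivery rates of 16% (control) and 25% (NRT), from Sample size. They are described there as cessation rates and are used here as stand-ins for validated abstinence.
- Postnatal restart: "around two thirds re-start post-natally", from Background. It describes pregnant smokers in general who stop for some part of pregnancy. One third are therefore taken to stay abstinent.
- f, the share of control-arm reported abstainers who fail CO: assumed 10%, 20% or 30%.
- k, the share of those women who go on reporting abstinence at 6 months: assumed 1 or 0.5.
- Equal misreporting probability among women in the two arms who did not truly quit: assumed.

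**Linked to the validated result.** 16%/3 = 5.33% and 25%/3 = 8.33%. The risk ratio is 8.33/5.33 = 1.56. Power with 525 per arm is 49%.

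**As written**
- Control misreporters: m = 0.16/(1 − f) − 0.16
- Misreporting probability: q = m/0.84
- NRT misreporters: 0.75 × q
- Literal 6-month rate: validated rate/3 + k × misreporters

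For f = 20% and k = 1: m = 0.16/0.80 − 0.16 = 0.040; q = 0.040/0.84 = 0.0476; NRT misreporters = 0.75 × 0.0476 = 0.0357. Control is 5.33% + 4.00% = 9.33%. NRT is 8.33% + 3.57% = 11.90%. The risk ratio is 1.28.

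| f | k | Control | NRT | RR | Control successes who had failed CO |
|---|---|---|---|---|---|
| 10% | 1 | 7.1% | 9.9% | 1.40 | 25% |
| 20% | 1 | 9.3% | 11.9% | 1.28 | 43% |
| 30% | 1 | 12.2% | 14.5% | 1.19 | 56% |
| 10% | 0.5 | 6.2% | 9.1% | 1.47 | 14% |
| 20% | 0.5 | 7.3% | 10.1% | 1.38 | 27% |
| 30% | 0.5 | 8.8% | 11.4% | 1.30 | 39% |

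At f = 20% and k = 1, the absolute difference moves from 3.0 to 2.6 points and power from 49% to 27%.

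**The case against.** The strongest reply is that self-report after birth is an openly stated choice. The Abstract says so, and every smoking secondary is labelled that way. A differently defined secondary outcome may classify the same woman differently. The definitions are one-line entries that cite an outside source for prolonged abstinence, and a full protocol or SAP could supply the link. The first part stands: post-birth self-report is not the error. The second does not remove the point, because the article states a criterion for these outcomes and, applied as written, that criterion can contradict the trial's own CO reading. This is more than an omitted detail.

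A reader might infer several stronger things that the documents do not support.
- *Women known to have smoked would be counted as abstinent.* The delivery form records "Smoked between quit date and delivery", so a woman who admitted smoking has that on file. The clearly exposed group is women who claimed abstinence but failed or lacked CO. Home visits for CO testing after one month and after delivery will reduce the number with no reading.
- *Reported abstinence would be higher at 6 months than at delivery.* The definitions allow it, but none of the scenarios above shows it. Control reaches 16.0% only at f = 40% with k = 1, and NRT is then 17.9%, well below 25%.
- *The cost-utility results would be distorted.* The Health economic analysis plan takes cessation immediately before delivery as its primary health outcome. It says only that longer-term modelling uses two-year data, and does not say that outcomes 2 or 4 feed it.
- *A false claim of benefit could follow.* Under equal misreporting the bias is towards no effect.

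**Conclusion.** The inconsistency holds on the published text and does not depend on any assumed figure: outcomes 2 and 4 span the validated period but do not use the validation. The consequence is overstated sustained abstinence and a relative effect diluted towards 1.

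The size is unknown. The range of 1.40–1.19 (all persist) or 1.47–1.30 (half persist), against 1.56, rests on assumed values of f and k, on equal misreporting in the two arms, and on a general-population restart figure applied to trial quitters. The absolute difference changes little, and power for these outcomes is only about 49% even when they are linked. The outcomes are secondary, so the primary analysis and sample size are untouched. The change is worth making because it is cheap and makes the smoking outcomes coherent with one another.

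**What to change.** Define outcomes 2 and 4 as meeting the full primary outcome, with CO validation at one month and at delivery, plus self-reported abstinence since delivery at each later questionnaire: 6 months for outcome 2; 6 months, 1 year and 2 years for outcome 4. Keep the self-report-only version as a supporting analysis under a distinct name.

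The CO readings are already collected at both pregnancy time points, so no new measurement is needed. The questionnaires must ask about any smoking since delivery, not only current status.

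The cost is twofold. Reported long-term rates will be lower. Truly abstinent women with a missed CO reading will count as failures through to 2 years, as they already do in the primary outcome. A sensitivity analysis that excludes from success only women with a CO reading at or above the cut-off, and leaves those with a missing reading to self-report, would show how much this matters.
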